### 3.10. Radiotherapy Schedule

SRT will be administered according to a risk-adapted protocol; size and location of the tumor will drive doses and fractionations (54 Gy/3 fractions, 55 Gy/5 fractions, or 60 Gy/8 fractions). Regardless of the dose-fractionation regimen, the treatment will be delivered on alternate days. For all patients, a 4-D CT simulation scan will be acquired. Respiratory gating will be used in cases with thorax motion > 7 mm in any direction. The gross tumor volume (GTV) will be defined as the tumor visible on CT and PET imaging, and an internal GTV will encompass the GTV from all phases of respiration. A planning target volume (PTV) margin of 5 mm will be applied. The prescription point will be approximately the 80% isodose line surrounding the PTV, with the requirement that 95% of the PTV will be covered by 100% of the prescription dose. 

### 3.11. Timing of Exams and Procedures

Timings and types of procedures are synthesized in Figure 1 and Table 1.

Screening phase. Inclusion and exclusion criteria will be evaluated during the screening phase.

Baseline phase. Thereafter, after signing the informed consent, a venous blood sample (10 mL) for the liquid biopsy (LB) will be collected coinciding with the routine assessment before the SRT start. Baseline visit (clinical history, clinical examination, PS ECOG, vital signs) and exams (including basal LB (LB-T1)) will also be carried out within 14 days before the SRT start. Blood count and clinical biochemistry will be performed at our local laboratories. The following parameters will be assessed: blood count with leukocyte formula, hemoglobin, platelets, total bilirurbin, AST, ALT, alkaline phosphatase, serum creatinine, total proteins, sodium, potassium, calcium, urea, lactic dehydrogenase, creatinine clearance, CEA, and CA19.9. Patient’s heart rhythm and conduction will be evaluated with ECG. The ventricular ejection fraction will be assessed with cardiac ultrasonography.All potentially childbearing women musthave a negative pregnancy test during the screening phase. If requested by the local ethics committee, the test can also be repeated during treatment. Barrier methods for anti-conception must be used by all patients throughout the duration of the study. FDG-PET and total-body computed tomography with iv contrast or, if contraindicated, magnetic resonance (MRI) abdomen and high-definition chest-computed tomography without iv contrast will be performed. 

Treatment phase. Clinical examination and evaluation of vital signs will be performed at each radiotherapy visit. Cardiological evaluation, CEA, CA19.9, and assessment of response to treatment will be performed after 40 days and 2 months from the radiotherapy start and, thereafter, every 3 months until progression. 

“Interval” phase. LB-T2 will be performed 40 days after major nodule irradiation coinciding with post-RT cell blood count and biochemical assessment along with CT total-body-scan and FDG-PET. Thereafter, the disease will be monitored every three months, and non-irradiated nodules will be treated in case of volumetric progression according to clinical practice in oligo-metastatic disease.

End-of-study phase. The study ends after LB-T2 assessment. 

Follow-up. Additional radiotherapy, surgery, or systemic treatment lines in case of appearance of new nodules or specific follow-up procedures will be applied at the discretion of the clinician responsible for the medical treatment. 

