### 2.5. Definition of “Genetic Regression”

In a previous study in lung-limited omCRC, we documented changes of KRAS status in metastatic formalin-fixed and paraffin-embedded (FFPE) tumor tissues compared to the primary ones (KRAS was mutated in primary tumor but not in subsequent metastases) [9]. These genetic trajectories were associated with a good prognosis as observed also in omCRC with liver-limited disease [65] and poly-metastatic CRC [66]. Therefore, we defined “genetic regression” as the loss of the genetic alterations in a specific key-driver gene from the primary tumor to the metastatic one (i.e., mutant KRAS (mutKRAS) in primary tumor→wild-type KRAS (wtKRAS) in metastases). This issue was opposed to “progressive” genetic trajectory (i.e., wtKRAS in primary tumor→mutKRAS in metastases) where the metastatic lesions gain genetic alterations advantageous for the tumor development [67]. RAS proteins (specifically, KRAS and NRAS) are small GTPases along the epidermal growth factor receptor (EGFR) pathway [68,69]. When activated by ligand/receptor binding, RAS protein releases GTP, binds to GTP, and, in turn, activates crucial kinases(i.e., RAF proteins, phosphoinositide 3-kinase (PI3K)-AKT, etc.) involved in several cancer-related phenomena (migration, survival, adhesion, growth, and differentiation) [70]. These data indicate that omCRC tumor clones may follow regressive genetic trajectories differing from those of cancer cells with poly-metastatic behavior.

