## 3. Trial Design

### 3.1. Objectives

#### 3.1.1. Primary Objective

The primary objective is to verify that SRT can induce regression of KRAS mutant clones into the entire metastatic mass in a clean model of oligo-metastatic CRC. 

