### 3.2. Design and Sample Size Calculation

PRELUDE-1 is a prospective, translational, and proof-of-principle study to detect regression of KRAS mutations in CRC induced by SRT. It will be conducted at the academic hospital Istituto Nazionale Tumori di Napoli, IRCCS “G. Pascale” in Naples (Italy). The sample size of the PRELUDE-1 study is based on the innovative hypothesis that radiation-induced immunity could induce regressive trajectories in metastases bearing KRAS oncogene mutations (i.e., mutKRAS→wtKRAS). 

According to the binomial test, considering a frequency of KRAS mutations of 50.0% (the study is not restricted to KRAS mutated patients) and assuming a probability of mutKRAS→wtKRAS of p_0_ = 0.0077 [9], with α = 0.05, 1-β = 0.60, p = the *a priori* success rate, and X = the number of patients with mutKRAS→wtKRAS, the final sample size is 25 patients. With the algorithm $P\left(X,N,p\right)=\left(\begin{array}{c} N\\ x \end{array}\right)p^{x}{\left(1-p\right)}^{n-x}$, the regressive trajectory is statistically relevant if mutations occurs in >2 out of the planned 25 patients.

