### 3.8. Bioinformatics Analysis and Data Presentation

An IlluminaTruSigth Oncology bioinformatics pipeline will be used to analyze DNA sequencing results. Number of reads and coverage in the target regions will be required to be above the manufacturer’s suggested thresholds. Sequence data will be aligned to the human reference genome GRCh37 (http://www.ncbi.nlm.nih.gov/projects/genome/assembly/grc/human/index.shtml) (accessed on 22 June 2021) through the Burrows–Wheeler Aligner with default parameters [78]. GENCODE, ICGC-PCAWG, dbNSFP, COSMIC, ClinVar, CancerMine, 1000Genomes, OncoScore, CIViC, and CBMDB databases will be used to assess the clinical significance of the found variants. The global minor allele frequency cut-off to filter and remove variants will be <1%. The four-tiered structure, designed by the joint consensus recommendation of the AMP/ACMG [79] will be applied to prioritize variants. However, to exclude residual false positives, variants will be also manually curated. The overall genetic evolution will be indicated with: (i) the percent of mutational concordance between different samples and (ii) Venn diagrams in order to plot intersections among genetic results in different samples (see beyond). Phenolyzer, a computational tool that prioritizes genes on the basis of updated existing knowledge (protein–protein interactions, the sharing of biological pathways or gene families, gene–gene transcriptional regulation, etc.), will be used to evidence relevance and relationships between any “seed” genetic variants and “secondary” ones [80]. 

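### KRAS conversion is read from plasma after SRT but tested against a tissue-derived null rate, with no stated check that tumor DNA is present, so the primary test can be positive without clonal regression

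*Protocol article*

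**What the plan says.** Section 3.1.1 sets the primary objective as showing that "SRT can induce regression of KRAS mutant clones into the entire metastatic mass". Section 2.5 defines genetic regression as the "loss of the genetic alterations in a specific key-driver gene from the primary tumor to the metastatic one", which compares two tissues.

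Section 3.2 bases the sample size on the hypothesis that "radiation-induced immunity could induce regressive trajectories in metastases bearing KRAS oncogene mutations". It takes KRAS mutations in 50% of patients, does not restrict entry to them, and sets the null rate by "assuming a probability of mutKRAS→wtKRAS of p_0_ = 0.0077 [9". With α = 0.05 and power 0.60 it arrives at 25 patients, and the result is relevant if more than 2 of 25 convert. The reference behind 0.0077 is the earlier study of which section 2.5 says "we documented changes of KRAS status in metastatic formalin-fixed and paraffin-embedded (FFPE) tumor tissues compared to the primary ones".

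The readout is different material. In section 3.11, "LB-T2 will be performed 40 days after major nodule irradiation coinciding with post-RT cell blood count and biochemical assessment", and the study then ends. Table 1 shows liquid biopsy at two times only: within 14 days before SRT (LB-T1) and 40 days after it (LB-T2). Section 3.4 collects FFPE tissue from the primary tumor, with none from metastases.

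On quality, section 3.4 assesses the concentration, quantity and integrity of cfDNA. Section 3.8 says "Number of reads and coverage in the target regions will be required to be above" the manufacturer's thresholds and adds manual curation of variants. Section 3.8 also plans percent concordance and Venn diagrams between samples on the 523-gene panel.

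**The concern.** A KRAS-mutant tumor can read as wild type in plasma for two reasons: the mutant clone has gone, or too little tumor DNA is in the tube to show it. The design makes the second reason plausible. Patients have two or three nodules of at most 25 mm, the largest has just been irradiated, and section 2.4 itself attributes ctDNA to release by tumor cells through apoptosis, necrosis and secretion.

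A null rate from tissue makes no allowance for this kind of non-detection. Total cfDNA quantity and integrity, reads and coverage show that the assay could run. They do not measure the tumor fraction. If lost signal counts as conversion, a positive primary result cannot separate immune elimination of mutant clones from direct killing of a shedding lesion by SRT or from low shedding. The primary question would then stay open after a nominally significant test.

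**Working it through.** **Inputs from section 3.2.** N = 25; KRAS-mutated share 0.50, so about 12.5 patients can convert; p0 = 0.0077; success if X > 2, that is X ≥ 3.

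**Assumed input.** f = share of KRAS-mutated patients whose variant is undetected at LB-T2 although the clone persists. The documents do not give f, so a range is shown.

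**Step 1: the plan's own rule under its own null.** P(X ≥ 3) = 1 − P(0) − P(1) − P(2), with X ~ Binomial(25, 0.0077):

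1 − 0.8243 − 0.1599 − 0.0149 = 0.0009.

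The article states no alternative rate, so N = 25 cannot be reproduced uniquely. With X ≥ 3, power of 0.60 corresponds to a rate of about 0.1215.

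**Step 2: no true regression, conversions only from lost signal.** The per-patient rate is 0.50 × f. Example for f = 10%: rate 0.05, and 1 − 0.2774 − 0.3650 − 0.2305 = 0.127.

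| f (assumed) | rate 0.50 × f | expected false conversions, 25 × rate | P(X ≥ 3 of 25) |
|---|---|---|---|
| 2% | 0.010 | 0.25 | 0.002 |
| 5% | 0.025 | 0.625 | 0.024 |
| 10% | 0.050 | 1.25 | 0.127 |
| 20% | 0.100 | 2.5 | 0.463 |
| 30% | 0.150 | 3.75 | 0.746 |
| 50% | 0.250 | 6.25 | 0.968 |

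The probability reaches 0.05 at a rate of 0.0335 (f about 6.7%) and 0.50 at a rate of 0.1055 (f about 21%).

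**Step 3: which samples are compared.** The article does not say whether conversion runs from FFPE primary to LB-T2 or from LB-T1 to LB-T2. In the first case a patient who never shed detectable DNA also adds to f. In the second, only patients with a KRAS mutation seen at LB-T1 can convert, and the rate becomes 0.50 × d × l, with d = detection at LB-T1 and l = loss by LB-T2 (both assumed):

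- d = 0.3, l = 0.2: rate 0.030, P(X ≥ 3) = 0.038
- d = 0.5, l = 0.3: rate 0.075, P(X ≥ 3) = 0.288
- d = 0.5, l = 0.5: rate 0.125, P(X ≥ 3) = 0.620

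Requiring detection at LB-T1 reduces the problem but does not remove it.

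**Step 4: is it enough to restrict the test to evaluable mutated patients?** No, if 0.0077 is kept. With 6 evaluable patients, P(X ≥ 1) = 1 − (1 − 0.0077)^6 = 0.045, so one conversion would be significant. With 12, P(X ≥ 1) = 0.089 and P(X ≥ 2) = 0.004. The null rate, denominator and cut-off have to be reset together.

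**The case against.** The strongest reply is that the article states no rule scoring an LB-T2 sample without ctDNA as wild type. It is a condensed account, and handling of uninformative samples may stand in the full protocol or a laboratory manual. That is right, and it limits the claim: such samples can be counted as conversions, but nothing shows that they will be.

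Second, everything in the size depends on f. At 2% or 5% the chance of a false positive (0.002 and 0.024) stays below the nominal 0.05, and it exceeds one half only above about 21%. A reader might infer that the test would be positive without regression. The documents support only that it could be.

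Third, the plan does have checks beyond reads and coverage: cfDNA concentration, quantity and integrity, and manual curation. The concordance and Venn outputs could also reveal whether other tumor variants persist. This stands as description. However, none of the checks measures tumor fraction, and the multi-gene comparison is descriptive and not linked to the KRAS call or the decision rule.

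Fourth, the documents do not say that the largest nodule supplies most of the ctDNA, and one or two untreated nodules remain. The point does not need that assumption, since f covers any cause of non-detection.

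One part is not answered by condensation. The tissue-based p0, the plasma readout and the rule of more than 2 in 25 are all stated in the article, and they do not fit one another. An unseen classification rule would not turn p0 into a plasma rate.

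**Conclusion.** The point holds as a mismatch between null rate, readout and decision rule, joined with an endpoint definition that does not separate undetectable ctDNA from wild-type KRAS. The nominal error rate therefore does not protect the primary conclusion.

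Against 0.0009 under p0, the chance of a positive result without clonal regression ranges from 0.002 to 0.968 for f from 2% to 50%. This rests on the protocol's 50% mutation frequency, independent patients, no true regression, and an f that the documents do not supply. Three lost signals among about 12.5 mutated patients are enough.

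The documents do not support the stronger readings that undetectable ctDNA is scored as wild type by rule, or that a false positive is the expected outcome. Because this is the primary endpoint and the basis of the sample size, it should be settled before LB-T2 results are read.

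**What to change.** In sections 3.2 and 3.8:

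1. **Fix the comparison pair.** KRAS mutation present in the FFPE primary and at LB-T1, then assessed at LB-T2.
2. **Require proof of tumor DNA.** Count mutKRAS→wtKRAS only if at least one other tumor-specific variant from the same panel is still detected at LB-T2, and KRAS depth is adequate to exclude the variant at the allele fraction those variants imply.
3. **Name the other outcome.** Otherwise class the patient as ctDNA not detected, not evaluable for regression, and report the number separately.
4. **Address the null rate.** State that 0.0077 makes no allowance for plasma non-detection, and either justify it for plasma or present the test over a range of plasma null rates.
5. **Restate the test.** Give cut-off, exact type I error and power for the evaluable KRAS-mutated patients, and do not carry over more than 2 of 25.

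No new samples or assays are needed, because the panel is already planned for these samples. It is still more than a change of wording: the primary test is re-specified, and the depth criterion needs an assay detection limit that the article does not give. The evaluable group will be at most about half of 25, so the stated power will fall, and the plan should say so.

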### 3.12. Response and Toxicity Assessment

Response will be assessed through total-body computed tomography (CT) with iv contrast (if contraindicated: abdomen MRI and high-definition chest-computed tomography without iv contrast), CEA, CA19.9, and PET-FDG after 40 days from the end of SRT. A CT scan will be repeated at two months and, thereafter, every three months until progression. RECIST v. 1.1 (https://recist.eortc.org/recist-1-1-2/) (accessed on 22 June 2021) will be applied to classify responses. An independent and blinded data monitoring committee (DMC) will review radiologic responses. The DMC will also review the PFS data. Toxicity will be evaluatedaccording to the CTCAE, version 4.0 (https://www.eortc.be/services/doc/ctc/CTCAE_4.03_2010-06-14_QuickReference_5x7.pdf) (accessed on 22 June 2021). The presence of eventual adverse events will be evaluated at each study visit. Patients will also notify the investigator by telephone in case of adverse events occurring between one visit and the next. The maximum grade per patient will be reported for each adverse event. A toxic effect of any grade on multiple occasions will be counted only once.

FDG-PET will be performed after 40 days from the treatment end to early monitor untreated nodules. In this case, tumor metabolic changes will be evaluated according to the European Organization for Research and Treatment of Cancer (EORTC) criteria [81,82]. Metabolic responses by FDG-PET/CT are defined as follows: Complete metabolic response (CMR), complete resolution of all metabolically active target and non-target lesions, and no new lesions;Partial metabolic response (PMR), 20% or greater decrease in SUV of target lesions with or without decrease in number/size of nontarget lesions, and no new lesions;Progressive metabolic disease (PMD), one or more new lesions, 20% or greater increase in SUV of target lesions, and/or unequivocal increase in FDG activity of nontarget lesions;Stable metabolic disease (SMD): not qualifying as CMR, PMR, or PMD.

### 3.13. Data Management

Clinical data will be registered in electronic case report forms (eCRFs). From a formal point of view, institutional standard operating procedures (SOPs) have been used to write and present this protocol to the ethical committee. Patient safety and integrity of the data are guaranteed by the strict adherence to SOPs (integral SOPs can be requested to [contact]). Audits and other monitoring procedures will be planned by the Director of Scientific Monitoring and Research Quality Assurance ([name] [name]). The Principal Investigator will be responsible to clarify or respond to any eventual queries coming from the sanitary authorities or any component of the scientific community. The clinical database will be locked and analyzed at the end of enrollment. 

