#### 3.1.2. Secondary Objectives

The most important secondary objective is the description of eventual radiologic responses in non-irradiated disease (abscopal effect). It will be measured through total-body computed tomography (CT) with iv contrast (if contraindicated: chest-computed tomography without iv contrast).

Other secondary objectives are the responses’ duration, progression-free survival (PFS), and toxicity (see beyond for response and toxicity assessment criteria). The response duration will be measured from the time of documented objective response until documented tumor progression. PFS will be determined from the data of treatment start until progression. Overall survival is generally long in this clinical setting so that it cannot be evaluated in the short time of the study. 

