### 3.14. Patients’ Study Withdrawals

Patients’ withdrawals from study will be registered in eCRFs. The information will include the date and the reason for cessation. However, considering the high translational nature, the short duration of the study, its small sample size, and the good safety profile of SRT, withdrawals are expected to be extremely low. Patients off study therapy will be followed-up until death. Patients stopping the treatment early for any reason will not be excluded from the progression-free survival analysis; all patients will be included in the descriptive statistics.

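### Locking the database at the end of enrollment precedes the 40-day assessments of the last patients, and the stated study end at LB-T2 conflicts with the follow-up that PFS and response duration need

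*Protocol article*

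**What the plan says.** **Lock.** Section 3.13 (Data Management): "The clinical database will be locked and analyzed at the end of enrollment". The article gives no other time for the primary analysis.

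**Post-treatment sample and study end.** Section 3.11: "LB-T2 will be performed 40 days after major nodule irradiation coinciding with post-RT cell blood count and biochemical assessment", together with total-body CT and FDG-PET. Section 3.12 and Table 1 count the 40 days from the end of SRT. The end-of-study paragraph of 3.11 then reads: "The study ends after LB-T2 assessment".

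**Endpoints that need longer follow-up.** Section 3.1.2 defines PFS from treatment start to progression and adds: "The response duration will be measured from the time of documented objective response until documented tumor progression". Section 3.12: "A CT scan will be repeated at two months and, thereafter, every three months until progression". In Table 1 the PFS row is first marked in the two-month column. Section 3.14: "Patients off study therapy will be followed-up until death".

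**The concern.** There are two separate problems.

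First, the lock is tied to the entry of patients, whereas the data to be analyzed arise six to ten weeks after entry. Anyone enrolled shortly before the lock has not reached the 40-day visit. That visit supplies the first response assessment, including the non-irradiated nodules in which the abscopal effect is sought, and the blood sample from which loss of mutant KRAS is judged. The design has 25 patients, a planned power of only 60% and a rule that needs at least three regressions, so it has little room for lost patients.

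Second, a study that ends at LB-T2 ends at the first response scan and before the first visit at which Table 1 marks PFS. Taken at its word, that sentence leaves no planned time in which to observe response duration or PFS, while other sections plan exactly that follow-up. The two cannot both govern.

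**Working it through.** **1. Time from entry to LB-T2.** Inputs: 3, 5 or 8 fractions (3.10), given on alternate days (3.10); LB-T2 40 days after the last fraction (3.12, Table 1); baseline tests up to 14 days before SRT start (3.11).

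First to last fraction = 2 × (fractions − 1) days. SRT start to LB-T2 = that span + 40. Opening of the baseline window to LB-T2 = a further 14 days at most.

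| Fractions | First to last | SRT start to LB-T2 | Baseline window opening to LB-T2 |
|---|---|---|---|
| 3 | 4 days | 44 days | up to 58 days |
| 5 | 8 days | 48 days | up to 62 days |
| 8 | 14 days | 54 days | up to 68 days |

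These are minimum treatment spans, with no missed days. The treatment-phase paragraph of 3.11 counts the 40-day response assessment from radiotherapy start instead. On that count the lag is 40 to 54 days, and the conclusion is the same.

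**2. Patients without LB-T2 at the lock.** Accrual time is not stated, so a range is assumed, with uniform entry. Expected number = (25 / accrual months) × (lag in days / 30.44).

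| Assumed accrual | Lag 44 days | Lag 68 days |
|---|---|---|
| 12 months | 3.0 | 4.7 |
| 18 months | 2.0 | 3.1 |
| 24 months | 1.5 | 2.3 |
| 36 months | 1.0 | 1.6 |

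This is about 1 to 5 of 25.

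**3. What that could cost in power.** Section 3.2 gives p0 = 0.0077, α = 0.05, power 0.60, N = 25 and a rule of more than 2 of 25, that is, at least 3. It gives no alternative rate p1, so N = 25 at 60% power can be neither reproduced nor refuted. The rule does hold α: with X ~ Binomial(25, 0.0077), P(X ≥ 3) = 0.0009.

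For illustration, solve P(X ≥ 3 | 25, p1) = 0.60. This gives p1 ≈ 0.121 (0.1215 unrounded). Hold that rate and the threshold of 3, and reduce N:

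| Evaluable patients | 25 | 24 | 23 | 22 | 21 | 20 |
|---|---|---|---|---|---|---|
| Power | 60.0% | 57.1% | 54.1% | 51.0% | 47.8% | 44.5% |

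**4. PFS and response duration under the two possible readings.**

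- *The follow-up schedule governs and only the lock applies.* Patients enrolled early have CT data up to the lock. Patients enrolled late are censored with little or no follow-up, and the censoring time is set by order of entry.
- *The study end at LB-T2 governs.* Response is first scanned at the LB-T2 visit, so response duration has essentially no observation time, and no visit that Table 1 marks for PFS lies inside the study.

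**The case against.** The case for leaving the text alone has real substance.

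- **Scope of the lock.** Section 3.13 speaks of the clinical database, in a paragraph about eCRF data. The KRAS result comes from stored plasma through a separate sequencing pipeline (3.4, 3.8), and the rule in 3.2 refers to all 25 planned patients. A reader might infer that late patients certainly lose the primary endpoint; the text does not establish that. It does not exclude it either, since the sentence also fixes when the data are analyzed and no other analysis time is given. The 40-day radiologic response is clinical data on any reading.
- **Meaning of the study end.** The sentence stands under an end-of-study heading, after text on three-monthly monitoring and before a follow-up paragraph. It can be read as closing only the sampling phase for each patient.
- **Observability.** A reader might infer that PFS and response duration cannot be observed at all. That is too strong: CT is planned until progression, the monitoring committee reviews PFS (3.12), and patients who stop early stay in the PFS analysis (3.14). Administrative censoring is also ordinary. What remains is immaturity in late patients.
- **Toxicity.** It would be wrong to say that late patients have no toxicity data. Patients are examined at each radiotherapy visit, adverse events are assessed at each study visit, and patients report events by telephone between visits. Only the later part is cut off.
- **Power.** A rule of at least 2 with p1 = 0.08 gives 60.5% at N = 25 and 50.9% at N = 21, but that is not this trial's rule. Under the stated rule p1 = 0.08 gives only about 32% at N = 25.

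**Conclusion.** The point holds in a limited form. The lock rule is stated, and if followed it precedes the 40-day assessments of the last patients by 44 to 54 days from SRT start, up to about 68 days from the opening of the baseline window. About 1 to 5 of 25 patients would lack the 40-day response at the lock. They would also lack LB-T2 unless the sequencing data are locked separately. This count rests on assumed uniform accrual over 36 to 12 months.

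The power loss, from 60% to between 57% and 44.5%, is illustrative. It rests on an implied p1 of about 0.121 that the article does not state, and on the affected patients dropping out of the primary analysis. Such a loss could change the decision; nothing in the article shows that it would.

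The study-end sentence contradicts 3.1.2, 3.12, 3.14 and Table 1 on its face. The benign reading is plausible, but the reader has to supply it. This is an internal inconsistency with a cheap remedy, to be settled before any lock.

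**What to change.** 1. In 3.13, lock the primary and response analysis, including the abscopal description, only after the last enrolled patient has completed LB-T2 and the two-month CT. State whether the sequencing results are locked at the same time.
2. Set a separate, later data cut for PFS and response duration, at a fixed follow-up after the last patient's SRT, so that order of entry no longer sets the minimum follow-up.
3. In 3.11, reword the study-end sentence so that LB-T2 closes the translational sampling phase only. Reconcile it with the CT schedule, the PFS row of Table 1 and the follow-up until death in 3.14.

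**Cost.** The changes are wording. The primary lock moves about two to three months later, and there is a second data cut to prepare and report. Sample size, assessments and visit schedule stay as they are.
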